## Abstract

**Background:**

Shoulder pain is a highly prevalent complaint and disorders of the rotator cuff, including tears, are thought to be the most common cause. The number of operations repair the torn rotator cuff has risen significantly in recent years. While surgical techniques have progressed, becoming less invasive and more secure, rehabilitation programmes have remained largely like those initially developed when surgical techniques were less advanced and more invasive. Uncertainty remains in relation to the length of post-surgical immobilisation and the amount of early load permitted at the repair site. In the context of this uncertainty, current practice is to follow a generally cautious approach, including long periods of immobilisation in a sling and avoidance of early active rehabilitation. Systematic review evidence suggests early mobilisation might be beneficial but further high-quality studies are required to evaluate this.

**Methods/design:**

RaCeR is a two-arm, multi-centre pilot and feasibility randomised controlled trial with nested qualitative interviews. A total of 76 patients with non-traumatic rotator cuff tears who are scheduled to have a surgical repair will be recruited from up to five UK NHS hospitals and randomly allocated to either early patient-directed rehabilitation or standard rehabilitation that incorporates sling immobilisation. RaCeR will assess the feasibility of a future, substantive, multi-centre randomised controlled trial to test the hypothesis that, compared to standard rehabilitation incorporating sling immobilisation, early patient-directed rehabilitation is both more clinically effective and more cost-effective. In addition, a sample of patients and clinicians will be interviewed to understand the acceptability of the interventions and the barriers and enablers to adherence to the interventions.

**Discussion:**

Research to date suggests that there is the possibility of reducing the patient burden associated with post-operative immobilisation following surgery to repair the torn rotator cuff and improve clinical outcomes. There is a clear need for a high-quality, adequately powered, randomised trial to better inform clinical practice. Prior to a large-scale trial, we first need to undertake a pilot and feasibility trial to address current uncertainties about recruitment, retention and barriers to adherence to the interventions, particularly in relation to whether patients will be willing to begin moving their arm early after their operation.

**Trial registration:**

ISRCTN Registry, 18357968. Registered on 10 August 2018.

**Electronic supplementary material:**

The online version of this article (10.1186/s13063-019-3407-3) contains supplementary material, which is available to authorized users.

## Background

Shoulder pain is a highly prevalent complaint and disorders of the rotator cuff (RC) are thought to be the most common cause [1]. Overall, the prevalence of RC abnormalities, including RC tears, increases with age, from 9.7% in patients under 20 years to 62% in patients over 80 years [2]. Typically, shoulder pain is initially treated using non-surgical means, including, for example, pain medication and physiotherapist-led exercise. However, if symptoms persist and the patient has a RC tear confirmed on a scan, then surgery might be considered [3]. In 2017/18, 18,237 patients with RC syndrome, including tears, were admitted to hospital in the UK’s National Health Service (NHS) [4].

Surgical techniques to repair the RC have progressed over time. They have become less invasive and the repairs have become more secure, raising the possibility of more rapid patient recovery [5, 6]. Despite surgical progression, our understanding of the optimal approach to post-operative rehabilitation, a critical component of the recovery process, is poor [6]. Rehabilitation programmes have remained largely like those initially developed when surgical techniques were less advanced and more invasive [7]. There is uncertainty about two related issues: (1) the length of post-surgical immobilisation and (2) the amount of early load permitted at the repair site [3]. In the context of this uncertainty, current practice is to follow a generally cautious approach, including long periods of immobilisation in a sling (of more than 1 month) and avoidance of active rehabilitation or movement [7], possibly due to fear of failure or re-tear of the repair site. However, such long periods of shoulder immobilisation impact significantly on patient’s quality of life, including their ability to care for themselves, drive and work.

Furthermore, long periods of immobilisation of the shoulder after surgery may result in stiffness and weakness and delay functional recovery, and, moreover, they may actually be detrimental to healing. Improved clinical outcomes, including reduced length of hospital stay, have been reported in other areas of orthopaedic and musculoskeletal rehabilitation with early mobilisation, for example for ankle sprains and joint replacements, without compromising healing [8, 9]. A systematic review and meta-analysis of 12 studies concluded that concerns about the early initiation of rehabilitation following RC surgical repair might not be warranted in terms of adverse patient-reported outcomes or tendon re-tear, but these trials were heterogeneous and too small to detect small to moderate differences between groups [10]. Seven of the 12 studies [9, 11–16] evaluated early versus delayed initiation of rehabilitation. Typically, this referred to initiation of passive range of movement exercise (i.e. with no or minimal load), with the exception of Klintberg et al. [9], who commenced low-level active range of movement exercises from day 2 post-operatively. These studies suggest that early initiation of rehabilitation does not adversely affect pain and disability outcomes in the short (3 months), mid (6 months) or long term (12 months). However, one randomised controlled trial (RCT), regarded as low quality due to lack of both allocation concealment and intention-to-treat analysis, suggested that early initiation of rehabilitation might favourably affect pain and disability outcomes in the short term (4 months) [13]. Five of the 12 studies [11, 12, 14–16] (*n* = 469) evaluated early versus delayed initiation of rehabilitation and reported outcomes in terms of rate of RC tendon re-tear. The pooled odds ratio of tendon re-tear in the early rehabilitation group was 1.3 (95% confidence interval: 0.72–2.2; *p* = 0.41), which suggests that patients undergoing early rehabilitation were slightly more likely to have a tendon re-tear than those in the delayed rehabilitation group but the difference was not statistically significant. Subsequent to the systematic review, a Canadian RCT (*n* = 189) compared early rehabilitation (patient-led mobilisation or movement of the shoulder) with sling immobilisation following RC repair [17]. This trial did not restrict inclusion by size of RC tear and concluded that the range of movement of the shoulder was better at 6 weeks in the early rehabilitation group, but there were no significant differences between groups at 3, 6, 12 or 24 months, indicating that early rehabilitation might result in a faster recovery without detrimental effects in the longer term. In addition, Mazuquin et al. [18] conducted a review of systematic reviews and concluded that early mobilisation might be beneficial but suggested more high-quality studies are required, especially for patients with large tears.

## Methods/design

This protocol is reported with reference to the SPIRIT checklist (Additional file 1) [19].

### Study design

The RaCeR study is designed as a two-arm, multi-centre pilot and feasibility RCT with nested qualitative interviews (Figs. 1 and 2).

**Fig. 1 Fig1:**
[figure not shown]
Study flow chart

**Fig. 2 Fig2:**
[figure not shown]
Schedule of enrolment, interventions, and assessments (SPIRIT Statement) [19]

### Aim

In patients undergoing surgical repair of the RC, we aim to assess the feasibility of a future, substantive, multi-centre RCT to test the hypothesis that, compared to delayed rehabilitation incorporating sling immobilisation, early patient-directed rehabilitation is both more clinically effective and more cost-effective.

### Objectives

The objectives of this pilot and feasibility RCT are as follows:To determine the availability of eligible patients and the rate of recruitment.To determine the rate of retention and the response rates to questionnaires and SMS text messages.To determine whether the interventions can be delivered per protocol, including an assessment of adherence, i.e. the time out of sling for both the early rehabilitation group and the sling immobilisation group.Determine the primary outcome measure for the main trial by evaluating sensitivity to change and assess other statistical properties related to clinical outcomes (e.g. standard deviation, betweenmeasurement correlations, event rate) that would be required to inform the sample size calculation for a main trial as well as an assessment of the completeness of follow-up between different methods of data capture (questionnaire and SMS text),Determine rate of response and completion of healthcare resource use questionnaire and productivity, including return to work,Explore participant satisfaction with interventions,Determine rate of tendon re-tear or failed healing (same outcome that RC is not intact) at 12-weeks post-surgery determined via diagnostic ultrasound,Determine number and nature of adverse events via self-report questionnaire.

Semi-structured qualitative interviews will be undertaken:To determine the acceptability of the interventions to patients and clinicians.To identify the barriers and enablers to adherence.To identify which outcome measures best reflects the participants’ rehabilitation goals.

### Study setting

Patients will be recruited from orthopaedic departments of the participating UK NHS hospitals. Following surgery to repair the RC, the study interventions will be delivered prior to discharge while the patient is on the hospital ward. Subsequent components of the study interventions will be delivered through outpatient physiotherapy settings in, or affiliated to, the main hospitals.

### Participants

#### Inclusion criteria

Patients can be included if they meet all of the following criteria:They have been diagnosed with a non-traumatic symptomatic tear of the RC and listed for surgical repair.They have RC tear that has been confirmed by ultrasound or magnetic resonance imaging (MRI).They are aged ≥18 years.They have been screened by a surgeon as suitable for participation.They can return to the recruiting centre or affiliated site for the initial outpatient follow-up physiotherapy appointment.They have access to a mobile phone and are willing and able to receive and respond to SMS text messagesThey understand English.

#### Exclusion criteria

Patients are excluded if they met any of the following criteria:They have a traumatic RC tear (e.g. sudden onset of shoulder pain and weakness following a fall). Given the different care pathways in the UK, such patients are typically fast-tracked to surgery.They unable to give full informed consent.

#### Recruitment

Potential participants will be identified from the surgical waiting list by a hospital-based research health-care practitioner (e.g. a nurse, physiotherapist or radiographer) and screened with reference to the inclusion and exclusion criteria. If potentially eligible, they will be sent in the post from the NHS hospital an invitation to participate in the study, an explanatory letter and a participant information sheet. These will include contact details of the research health-care practitioner. They will then be followed up by the research health-care practitioner within approximately 1 week by telephone (up to three attempts) or at a different time if the patient wishes to initiate the telephone call. If during screening including the telephone call, the patient indicates an interest in being involved or wishes to have further time to consider, they will be invited to discuss participation in the study further with the research health-care practitioner at the time of the pre-operative clinic appointment or another convenient time. For patients who cannot be contacted over the telephone, a follow-up letter will be sent asking them to make contact with the research health-care practitioner at the time of their pre-operative assessment should they be interested.

This discussion will build on a recent successful six-step model to promote recruitment to RCTs that resulted in 57% recruitment of eligible patients in an orthopaedic setting [20], and will include: (1) an explanation of the condition, (2) reassurance about receiving treatment, (3) telling the patient about the uncertainty in what is the most effective approach to rehabilitation to highlight reasons why the research is necessary, (4) an explanation of the purpose of the study, (5) a balanced view of the two interventions after surgery and (6) an explanation of study procedures including randomisation and follow-up requirements. This process will be supported by a recruitment script written for the research health-care practitioner, which they can refer to during both the initial telephone call and the subsequent pre-operative clinic appointment.

During the telephone call, medical note review and face-to-face meeting, the patient’s age and year of birth, gender, diagnosis, size and location of RC tear and, if applicable, reason for exclusion will be collected. Once patients have been identified, and it is confirmed that they have a symptomatic RC tear and are 18 years or older, the research health-care practitioner will check their medical notes to confirm that the surgeon responsible for their care does not wish them to be excluded from participation in the study prior to contacting them. This checking process will be documented.

Interested and eligible patients will be required to provide written informed consent before participating. Typically, written informed consent will be sought at the time of the pre-operative assessment or other convenient time prior to surgery. A research health-care practitioner, who will have received appropriate training and is authorised on the trial delegation log, will take informed consent. A record of the consent process will be kept in the patient’s medical records. The original consent form will be retained in the study site file and a copy will be given to the participant. A copy will also be securely sent to Keele Clinical Trials Unit (CTU) for monitoring purposes.

Participants have the right to withdraw at any time without any consequence to any future care they may require. For each trial participant, their general practitioner will be sent a letter from Keele CTU to confirm that their patient is taking part in the research study.

### Data collection

The research health-care practitioner will provide the baseline questionnaire to consenting patients for them to complete themselves. This collects demographic data, general practitioner details, the Oxford Shoulder Score (OSS), the Shoulder Pain and Disability Index (SPADI) and EQ-5D-5L. The patient will be given adequate time and a suitable location to complete the baseline questionnaire. It will be checked for completeness by the research health-care practitioner. The original baseline questionnaire will be sent to Keele CTU and a copy retained in the study site file. Once the baseline questionnaire has been completed and checked, the participant will be randomised to either the intervention or control group.

The size and location of the tear will be recorded, since these may be important determinants of the clinical outcome. This information will be collected by the research health-care practitioner from the pre-operative imaging, ultrasound scan (USS) or MRI, which will typically be available in the medical notes. Due to concerns about the reliability of measurements of the size and location of a tear by imaging alone, the physiotherapist who delivers the allocated treatment will record the intra-operative findings of the size and location of the tear and the completeness of repair as they will typically have access to this information. The completeness of the repair will allow the study team to contextualise the USS 12 weeks post-operatively. Previous studies have been criticised for reporting re-tears only dichotomously, i.e. torn or not, whereas a re-tear identified on an USS might just reflect that the tear was only partially repaired or not repaired at the time of the operation.

The OSS is a 12-item shoulder-specific self-report measure of shoulder pain and function, primarily used to assess the outcome of shoulder surgery in RCTs [21]. The OSS is reliable, valid, responsive and acceptable to patients [21–23]. The items refer to the past 4 weeks. Each has five ordinal response options scored from 0 to 4, with 4 representing the best outcome. When the 12 items are summed, this produces an overall score ranging from 0 to 48, with 48 being the best outcome.

The SPADI is a self-report measure of pain and function in patients with shoulder disorders [24]. It is the most commonly used outcome measure in trials of conservative interventions [25]. The SPADI has been validated for use with patients who have shoulder pain. A minimally clinically important change of 10 points has been identified [24, 26]. Additionally, excellent levels of reliability (intraclass correlation coefficient 0.66 to 0.95), high internal consistency (Cronbach’s α typically >0.9) and responsiveness over time have been reported in tandem with no floor and ceiling effects [26]. The SPADI has 13 items divided into two sub-scales: pain (5 items) and disability (8 items). The responses are indicated on a visual analogue scale where 0 = *no pain/no difficulty* and 10 = *worst imaginable pain/so difficult it requires help*. The items are summed and converted to a total score out of 100 where a high score indicates greater pain and disability.

The EQ-5D-5L is a generic measure of health-related quality of life. It provides a single index value for health status that can be used in a clinical or health economic evaluation [27]. The EQ-5D-5L consists of questions relating to five health domains (mobility, self-care, usual activities, pain/discomfort and anxiety/depression) and respondents rate their degree of impairment using five response levels (no problems, slight problems, moderate problems, severe problems and extreme problems) [27]. The EQ-5D-5L is the National Institute for Health and Care Excellence’s preferred measure of health-related quality of life in adults.

A patient-completed personal exercise diary will be returned to the treating physiotherapist at the 4-week follow-up appointment and then returned to Keele CTU. Alternatively, it can be returned to Keele CTU along with the 6-week postal questionnaire, if necessary.

The rate of tendon re-tear or failed healing will be evaluated through a diagnostic USS performed at 12 weeks according to an agreed and standardised protocol for the sonographers. This information will be compared to the pre-operative imaging results and the intra-operative findings. A diagnostic USS is regarded as a relatively cheap but accurate modality for identifying RC tears [28].

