#### Interventions

##### Control group

Reflective of current UK practice [7], after surgery, the patient’s shoulder will be immobilised using a sling for 4 weeks. They will have one session in the hospital with a physiotherapist, after surgery but prior to discharge. This session will include advice to maintain the sling in situ at all times. It should be removed *only* to perform specific daily exercises (table slides, active elbow, wrist and hand exercises and passive shoulder abduction, flexion and lateral rotation movements, within pain limits), or for eating, washing and dressing. The sling should also be worn at night. No further active movement will be encouraged. A post-operative information and exercise booklet with photographs and text detailing the exercise type and number of sets and repetitions will be provided. This initial discussion will be followed up approximately 2 weeks later at an outpatient appointment with the physiotherapist, who will reconfirm this advice.

Adherence to the programme, i.e. time out of the sling, will be measured using a personal exercise diary. This was developed in association with our patient and public involvement and engagement (PPIE) group and will be provided by the physiotherapist. Participants will be asked to record in the diary for how long they were not wearing the sling at regular periods throughout the day, in the same way as the intervention group. Participants will also be asked to record the extent to which they feel they have adhered to the prescribed exercise plan.

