### Sample size calculation

Although RaCeR is a pilot and feasibility RCT, a sample size calculation has been conducted to ensure there is a sufficient number of participants to detect a difference in time out of sling between the two randomised groups. Understanding this is a key feasibility objective and will be an important factor in determining whether a future main trial is feasible. Randomising 76 participants, which allows for 20% missing adherence-related data (time out of sling captured using the personal exercise diaries), will provide 90% power to allow us to detect at least a minimum 40% difference in sling use between the two arms, given a 1-sided 5% significance level. Randomising 76 participants will enable us to estimate the 1-sided lower 90% confidence limit for the follow-up rate to within about 6% of the anticipated 80% level. Further, a sample size of about 76, allowing for dropouts, will be sufficient to allow precise calculation of estimates of the standard deviations around potential primary clinical outcomes for a future main trial [29].

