### Statistical analysis plan

As this is a pilot and feasibility RCT, the main analysis will focus on process outcomes and will estimate the number of potentially eligible patients, the number and rate of eligible patients, the consent rate, the overall uptake rate (in relation to the number potentially eligible), the retention rate, follow-up rates for questionnaires and texts, and adherence to the interventions, including time out of sling. We will calculate means and confidence intervals of clinical outcomes (both within- and between-study groups) and determine which outcomes are most sensitive to change. We will evaluate the parameters required to inform the sample size calculation for a future main trial. A detailed statistical analysis plan will be developed by the study statistician and agreed by the trial steering committee.

At the end of the study, we will review the findings and in discussion with the trial steering committee, we will make a recommendation about proceeding to a future main trial. The following success criteria will be used to decide whether to make an application for funding for a main trial:i.)Recruitment rates: Randomisation after consent of 20% or more of eligible patientsii.)Intervention adherence: Difference in time out of sling of 40% or more, i.e. the early rehabilitation (intervention) group will report 40% more time out of the sling than the control group in the first 4 weeks after surgeryiii.)Follow-up rates for the potential main outcome measures >70% for questionnaires at 6 and 12 weeks and weekly for the SMS text messages

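### Time out of sling rests on one diary collected only after the 4-week window; the 20% allowance covers lost numbers, not selective non-return

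*Protocol article*

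**What the plan says.** The protocol article measures sling time with a diary in both arms. For the control group: "Adherence to the programme, i.e. time out of the sling, will be measured using a personal exercise diary". The Intervention group section uses the same instrument. The feasibility outcomes also name physiotherapist case report forms for fidelity and adherence, but tie time out of sling to the diaries. The weekly text messages cover pain and activity interference, not sling use.

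Collection is described under Data collection: "A patient-completed personal exercise diary will be returned to the treating physiotherapist at the 4-week follow-up appointment and then returned to Keele CTU". The next sentence adds a fallback: "Alternatively, it can be returned to Keele CTU along with the 6-week postal questionnaire, if necessary".

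The measure feeds the second success criterion: "Difference in time out of sling of 40% or more", explained as "the early rehabilitation (intervention) group will report 40% more time out of the sling than the control group in the first 4 weeks" after surgery. The sample size section calls sling use a key feasibility objective and allows for loss: "Randomising 76 participants, which allows for 20% missing adherence-related data (time out of sling captured using the personal exercise diaries". The eligibility criteria require attendance only for the first outpatient visit: "They can return to the recruiting centre or affiliated site for the initial outpatient follow-up physiotherapy appointment". Both arms have an outpatient physiotherapy appointment about 2 weeks after the in-hospital session.

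**The concern.** Both return routes come after the 4 weeks being measured, and both need a participant who has kept the diary and is still in contact. Someone who disengages in week 3 may have two good weeks of entries that never reach the trials unit. The 2-week appointment, where those entries could be secured, is not described as a collection point.

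Return of the diary may be related to what the diary measures. An intervention participant who could not give up the sling, or a control participant who abandoned it, may be less inclined to hand in a record showing this. If so, the difference among returned diaries would be larger than the difference among all randomised. Inflating the sample for missing diaries restores the number analysed; it does not make those who return them representative.

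Whether patients will move the arm early is the uncertainty that the article singles out for this pilot. A contrast measured on a selected subset could support an application for a main trial whose arms differ less in practice than the pilot suggested.

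**Working it through.** **Step 1. Reproduce the planned size.** The article gives 76 randomised, 1:1, 90% power, a one-sided 5% level, a 40% difference and 20% missing. It gives no arm-specific rates and no standard deviation. Assume rates of 30% and 70%.

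- Uncorrected: n = [1.645 × √(2 × 0.5 × 0.5) + 1.282 × √(0.3 × 0.7 + 0.7 × 0.3)]² / 0.4² = (1.163 + 0.831)² / 0.16 = 24.8 per arm.
- Continuity correction: (24.8 / 4) × [1 + √(1 + 4 / (24.8 × 0.4))]² = 29.6, so 30 per arm.
- Inflation: 30 / 0.8 = 37.5, so 38 per arm and 76 in total.

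The stated figure is reproduced under these assumed rates. With 20% and 60%, or 40% and 80%, the same method gives 74; with 10% and 50%, or 50% and 90%, it gives 66. In this calculation the 20% enters only as a divisor on the number analysed. It means 0.2 × 38 = 7.6, or about 8 diaries per arm, may be missing.

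**Step 2. Effect of selective non-return.** Read the criterion as percentage points (an assumption; the article does not say). Let the observed difference among returned diaries be exactly 40. Let a fraction m of intervention diaries be missing, and let those participants have s points less time out of sling than intervention returners. Control non-returners are taken to resemble control returners. Then:

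difference for all randomised = 40 − m × s.

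Setting missing intervention participants to the control level means s = 40:

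| Missing (m) | All-randomised difference |
|---|---|
| 10% | 40 − 4 = 36 |
| 20% | 40 − 8 = 32 |
| 30% | 40 − 12 = 28 |

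At m = 20%, milder shortfalls of 10, 20 and 30 points give 38, 36 and 34.

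**Step 3. Losses in both arms.** If the same fraction of control diaries is missing and those controls spent s points more time out of the sling than control returners, the difference is 40 − 2 × m × s. At m = 20% and s = 10, 20, 30 and 40 this gives 36, 32, 28 and 24.

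**Step 4. The other direction.** If the missing intervention participants used the arm more freely than returners, say by 20 points, the difference is 40 + 0.2 × 20 = 44, and the diary understates the contrast.

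**Step 5. Margin needed.** Under the control-level bound with 20% missing, an observed difference of 40 / 0.8 = 50 points corresponds to 40 for all randomised.

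All values of m other than 20%, and all values of s, are assumptions.

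**The case against.** The strongest reply is that the plan has a fallback. Posting the diary with the 6-week questionnaire requires neither attendance nor adherence. A reader might infer that anyone who stops the programme or misses the 4-week visit is lost from the measure. The article does not support that: only participants who miss both routes are at risk, and nothing says that a withdrawn participant's diary is discarded. This part of the objection stands.

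A reader might also infer that the reported contrast must be too large. That is not established either. The 4-week appointment starts routine physiotherapy in both arms, and an intervention patient who keeps the sling on is behaving much as the control advice asks, so there is no stated reason for that patient to stay away. Fast recoverers might equally stop recording. This too stands.

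Further points carry some weight. The content of the case report forms is not shown, so sling use may be noted at 2 weeks. The handling of missing or partial diaries belongs in the analysis plan that the article promises, and its absence here is no fault. Criterion ii is not a mechanical trigger: the findings go to the trial steering committee with two other criteria, and interviews at around 4 weeks give separate evidence on adherence.

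What remains is a matter of collection. An analysis plan cannot recover entries that never reached the trials unit. The fallback also relies on the 6-week questionnaire, for which the plan's own success threshold is only a follow-up rate above 70%, and diary return is not named in that criterion.

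**Conclusion.** The point holds as a weakness in data collection that is cheap to repair, not as an error or contradiction in the protocol. One self-completed diary, collected only after the 4-week window, is the sole stated source for a criterion on which the recommendation partly rests, and the 20% allowance addresses power alone.

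The size cannot be read from the article. With 20% of intervention diaries missing and those participants at the control level, an observed 40 points becomes 32 for all randomised. Milder assumptions give 34 to 38, and opposite deviations in both arms give 24 to 36. These figures assume that the criterion is in percentage points, that the observed difference sits exactly at the threshold, and that non-returners are less adherent. The last is plausible but not shown, and the reverse would raise the figure above 40. With an observed difference of 50 or more, the control-level bound at 20% missing would not change the decision.

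**What to change.** Issue the diary in two 2-week parts. Collect or copy the first part at the 2-week outpatient appointment already scheduled in both arms, and keep the 4-week and postal routes for the second. That appointment is also the one for which eligibility already requires that the patient can return. Collection there still depends on attendance, but it gives an additional and earlier chance to secure entries.

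Judge criterion ii on all participants with any sling data, and report beside it the diary return rate by arm and a bound that sets missing intervention diaries to the control level. Because arm use in the intervention group is meant to increase over time, show the two halves separately so that first-half data are not taken for the full 4 weeks. If the analysis plan already contains these items, only the collection change is needed.

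The cost is a reprinted diary, slightly more handling at the 2-week visit and a short amendment. A sling item in the weekly texts for weeks 1 to 4 is optional: it would reach non-attenders, but the prompts may influence sling use. The attendance criterion should stay as it is. Extending it to week 4 would narrow eligibility in a trial that is testing recruitment, and the postal route already serves those who cannot attend.
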